**Methods:**

The trial is designed to test the hypothesis that, compared to those receiving usual care plus a treatment with low-strength static magnets (attention-control complementary therapy), subjects receiving usual medical care plus CST will demonstrate significant improvement in: quality-of-life as measured by the Headache Impact Test (HIT-6); reduced frequency of migraine; and a perception of clinical benefit. Criteria for inclusion are either gender, age > 11, English or Spanish speaking, meeting the International Classification of Headache Disorders (ICHD) criteria for migraine with or without aura, a headache frequency of 5 to 15 per month over at least two years. After an 8 week baseline phase, eligible subjects are randomized to either CST or an attention control intervention, low strength static magnets (LSSM). To evaluate possible therapist bias, videotaped encounters are analyzed to assess for any systematic group differences in interactions with subjects.

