### Randomization

Subjects are randomized to one of the two treatment arms using a concealed allocation protocol. At the subject's first treatment visit, the study therapist performs a brief intake interview and then opens an opaque, sequentially numbered envelope that identifies which treatment group has been randomly selected for this subject. The randomization scheme uses a permuted block method to generate the intervention assignment sequence being implemented at the treatment location to assure that the randomization balance is maintained throughout enrollment [24].

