### Outcome measures and study instruments

#### Primary outcome variables

The primary outcome variables assessed for this study include headache-specific quality-of-life, frequency of headache and self perceived benefit of the intervention (Table 3 describes measurement points for these variables). Detailed descriptions of these variables follow:

**Table 3 T3:** Summary of Measures and Timing of Administration for Clinical Feasibility Trial of Craniosacral Therapy, 2006–2008

	**Week 0**	**Weeks 1 to 8**	**Weeks 8 to 16**	**Weeks 16 to 20**
**Variable or Instrument**	**Baseline Assessments**	**Baseline with Usual Care**	**Usual Care plus CST or LSSM**	**Post-treatment Assessments**

Demographic/Clinical Data	Week 0			
	ICHD* Diagnosis	Week 0		
Functional status – MOS SF-36	Week 0			Week 20
Expectation of benefit/Credibility †			(post 1^st^ treatment)	
Headache QOL – HIT-6 §	Week 0	Week 8		Week 16
Headache Diary: Frequency		Daily	Daily	
Perceived clinical change		Week 8		Week 16
Headache disability – MIDAS #	Week 0			Week 20
Headache Diary: Intensity and Duration		Daily	Daily	Daily
Headache Diary: Medication Use/Cost		Daily	Daily	Daily
Headache Diary: Health care visits		Daily	Daily	Daily
Satisfaction with care	Week 0	Week 8		Weeks 16, 20
Blood pressure and heart rate	Week 0		Weekly	
Therapist – Subject Interaction Analysis Videotaping Encounters**			Weeks 9,11, 13 & 15	

* International Classification of Headache Disorders, defined by expert members of the International Headache Society

† Based on a measure developed by Borkovec and Nau to measure credibility of psychological interventions [38,39].

§ Headache Impact Test was developed to measure headache-related quality of life [33].

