#### Headache Impact Test (HIT-6)

Headache-specific quality of life is measured as the change in headache-related disability at 8 weeks after randomization as assessed by the HIT-6. The HIT-6 is a validated questionnaire designed "to measure the impact headaches have on a person's ability to function on the job, at school, at home, and in social situations" [30]. It has good internal reliability [31]. The scale consists of six items that cover various content areas relevant to headache-related disability: pain, social functioning, role functioning, vitality, cognitive functioning, and psychological distress. A decrease of 2.3 HIT points (95% CI, 0.3 to 4.3) over six weeks among patients with chronic headache corresponds to a "somewhat better" self-reported rating on a global clinical change scale [31].

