#### Analytic Strategy

Sample size and power calculations are based on the assumptions regarding the changes under treatment in two key measures of interest, namely, quality of life as measured by the Headache Impact Test (HIT) and headache frequency based on headache diary. Preliminary studies [41] have shown a mean HIT score of 63.7 with a standard deviation of 5.2 among migraine patients. Keeping the control values of HIT at this level, we estimate that with 45 subjects in each arm the study will have 80% power to detect a 3.5 points change in the HIT score. Based on our clinical experience we also estimate that, on average, migraine patients experience two headaches per week. With 45 patients per group, the study will have 80% power to detect a reduction in the headache frequency to one per week.

Regression modeling strategies will be used to test the primary hypothesis. A simple linear regression model with the HIT score at end of the study (16 weeks) controlling for HIT score at the baseline will be used to test for significant treatment effects. We will use repeated measures analysis on HIT measures to detect whether the change in HIT scores are significantly different between the two groups. Because of the correlated nature of the repeated measures, regression models using a generalized estimating equations (GEE) approach will be used to test the hypothesis of change. A significant time and treatment interaction will detect significant changes in the score. A similar analysis strategy using GEE methods will be used to analyze daily records of headache. All data analysis will be performed on an intent-to-treat basis. The GEE method assumes that missingness in data are completely at random. Under the missing at random assumption, it is possible to conduct analysis using multiple imputation procedures [42].

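### HIT-6 has two unranked tests: a week-16 regression on an unidentified baseline, and a time-by-treatment interaction for which two of the three visits precede randomisation

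*Protocol article*

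**What the plan says.** The Analytic Strategy section gives two analyses of HIT-6 under the heading of testing the primary hypothesis.

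- The first, listed as the test for treatment effects, is "A simple linear regression model with the HIT score at end of the study (16 weeks) controlling for HIT score at the baseline". This is an analysis of covariance (ANCOVA).
- The second follows directly: "We will use repeated measures analysis on HIT measures to detect whether the change in HIT scores are significantly different between the two groups". It is to be fitted by GEE, and its criterion is that "A significant time and treatment interaction will detect significant changes in the score".

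The section does not rank the two. It does not say how time is coded or which visit supplies the baseline score. A similar GEE strategy is then carried over to the daily headache records.

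Table 3 (row "Headache QOL – HIT-6") schedules the questionnaire at weeks 0, 8 and 16. The abstract's Methods paragraph says "After an 8 week baseline phase, eligible subjects are randomized to either CST or an attention control intervention". Under Randomization the therapist, at the first treatment visit, "opens an opaque, sequentially numbered envelope that identifies which treatment group has been randomly selected for this subject". The HIT-6 section defines the endpoint as "change in headache-related disability at 8 weeks after randomization as assessed by the HIT-6".

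**The concern.** There is one endpoint and one time point at which the arms can differ, but two tests that can give different answers. If the choice between them is open when the data are seen, the nominal 5% error rate is no longer assured, and the published result may depend on which test is put forward. The open baseline adds a further choice.

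The interaction is also an awkward tool for this schedule. Weeks 0 and 8 are both before allocation, so no treatment effect can exist at either. A linear time term gives no weight to week 8, the score closest to randomisation. A categorical time term spends one of its two degrees of freedom on a contrast that is null by design. An ANCOVA can use both earlier scores to reduce variance.

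**Working it through.** **Inputs from the document.** HIT-6 at weeks 0, 8 and 16 (Table 3). SD 5.2, 45 per arm and a planned difference of 3.5 points (Analytic Strategy). A 2.3-point change as a smaller effect of interest (HIT-6 section).

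**Assumptions.** Two-sided 0.05, equal SD at every visit, complete data, an effect at week 16 only, and a common correlation r between any two visits. The document gives no r. Values from 0.3 to 0.8 were tried, with a first-order autoregressive pattern as a variant.

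**The plan's own figure.** An unadjusted comparison has SE = 5.2 × √(2/45) = 1.096. For 3.5 points, 3.5/1.096 = 3.19, and power = Φ(3.19 − 1.96) = 89.1%. The stated 80% is not reproduced from these inputs. An unstated allowance could explain it: 35 per arm gives 80%, and 35/(1 − 0.22) = 45. That is a separate matter and does not affect this point.

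**Step 1, timing.** Table 3 places the week-8 HIT-6 in the usual-care baseline column. Sessions 1, 3, 5 and 7 are videotaped (Quality control), and Table 3 dates the taping to weeks 9, 11, 13 and 15. The first treatment visit, where allocation is revealed, therefore falls in week 9. Weeks 0 and 8 precede randomisation and only week 16 follows it.

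**Step 2, variance per subject.** SD² = 27.04.

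| Analysis | Formula | r = 0.5 |
|---|---|---|
| ANCOVA, weeks 0 and 8 | SD²(1 − 2r²/(1 + r)) | 18.0 |
| ANCOVA, one baseline | SD²(1 − r²) | 20.3 |
| Interaction, pre/post time | 1.5 SD²(1 − r) | 20.3 |
| Interaction, linear time (week 16 minus week 0) | 2 SD²(1 − r) | 27.0 |

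At r = 0.5 the linear interaction has 27.0/18.0 = 1.50 times the variance of ANCOVA on both baselines, and 27.0/20.3 = 1.33 times that of ANCOVA on one. The categorical interaction is a 2-df test, handled with a noncentral chi-square.

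**Step 3, power.** SE = √(2V/45), power = Φ(δ/SE − 1.96). Example, linear interaction at r = 0.5 and 2.3 points: SE = √(2 × 27.04/45) = 1.096, 2.3/1.096 = 2.10, power 55.5%.

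| Power (%) | 2.3 pts, r = 0.3 | 0.5 | 0.7 | 3.5 pts, r = 0.3 | 0.5 | 0.7 |
|---|---|---|---|---|---|---|
| ANCOVA, both baselines | 61.8 | 72.9 | 89.7 | 93.1 | 97.4 | 99.8 |
| ANCOVA, one baseline | 59.5 | 67.8 | 83.6 | 91.7 | 95.8 | 99.4 |
| Interaction, pre/post | 53.5 | 67.8 | 87.9 | 87.6 | 95.8 | 99.7 |
| Interaction, categorical (2 df) | 43.3 | 57.4 | 80.6 | 80.3 | 92.0 | 99.3 |
| Interaction, linear | 42.6 | 55.5 | 77.3 | 77.0 | 89.1 | 98.5 |

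Under the autoregressive pattern (adjacent-visit correlation 0.7, 2.3 points), ANCOVA on week 8 or on both scores has 83.6% power. ANCOVA on week 0 has 67.3%, the pre/post interaction 73.3%, the categorical 68.8% and the linear 54.7%. So the unnamed baseline can matter as much as the choice of test.

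**Step 4, two answers.** 20,000 simulated trials per setting, using t and F forms of the tests. Each test alone rejects in 4.7–5.3% of null trials.

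| Null trials with either test significant (%) | r = 0.5 | r = 0.7 |
|---|---|---|
| Week-8 ANCOVA or linear interaction | 9.0 | 8.7 |
| Week-8 ANCOVA or categorical interaction | 8.5 | 7.8 |
| Week-0 ANCOVA or linear interaction | 7.4 | 6.4 |

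| Trials in which week-8 ANCOVA and interaction disagree (%) | r = 0.5 | r = 0.7 |
|---|---|---|
| 2.3 points, linear / categorical | 30.6 / 22.0 | 22.6 / 14.1 |
| 3.5 points, linear / categorical | 11.6 / 7.3 | 2.1 / 1.1 |

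Simulation error on a 9% rate is 1.96 × √(0.09 × 0.91/20,000), about 0.4 percentage points.

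**The case against.** A reader might infer that the interaction is the trial's decision test. The text does not support that. The ANCOVA comes first and is the one assigned to detecting treatment effects, so the type of analysis recommended here is already planned. What the text lacks is a ranking.

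A reader might also infer that the interaction wastes power whatever its form. Time coding is not stated. Under equal correlation, a pre/post contrast, which suits a two-phase design, equals one-baseline ANCOVA at r = 0.5 and beats it above. At the planned 3.5 points the linear form reaches 80% once r is about 0.35, and at r = 0.7 it loses about one percentage point against one-baseline ANCOVA. The 2.3-point figure is a six-week change among chronic-headache patients, not the between-arm difference used for sample size. All of this stands, and the loss is therefore stated as conditional.

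Nor do the pre-randomisation visits bias the interaction. For the diary, the article speaks only of a similar GEE strategy. It states no straight-line slope across the baseline weeks, so a fault there cannot be asserted.

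Finally, an article condenses a fuller document that may settle time coding and the baseline visit, and the endpoint wording leans towards week 8. But the article itself puts forward two tests for one primary hypothesis and gives neither precedence. The feasibility aims lower the stakes without removing them: the Hypothesis section states an efficacy hypothesis, and the Discussion plans to take effect sizes from these analyses for a larger trial.

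**Conclusion.** The point holds as one of unranked tests with an unidentified baseline, and it should be fixed. At r = 0.5 an either-test claim carries about 7–9% type I error. The week-8 ANCOVA and the interaction disagree in about 22–31% of trials at 2.3 points and 7–12% at 3.5 points. The article does not say it would claim success on either test, so the 7–9% is what the open choice permits, not a stated rule.

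The efficiency loss is secondary and conditional on linear or categorical time. At r = 0.5 and 2.3 points it is 10 to 12 percentage points against one-baseline ANCOVA and 15 to 17 against both baselines. It shrinks at higher correlation and at 3.5 points. ANCOVA on both earlier scores was at least as powerful as every interaction coding in all settings tried. The figures rest on the protocol's SD and sample size, an assumed alpha, assumed correlations and complete data.

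**What to change.** Name one primary HIT-6 analysis: week-16 HIT-6 regressed on arm, with the week-0 and week-8 scores (or their mean) as covariates, testing the single-degree-of-freedom arm effect. Label the GEE time-by-treatment interaction supportive. If it is kept, state the coding of time and constrain the arms to be equal at weeks 0 and 8.

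For the diary, state how time enters the model. If it would be a linear slope through the baseline weeks, compare treatment-phase days between arms instead, adjusted for each subject's baseline-period rate.

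The cost is analysis wording only. Both baseline scores are already scheduled and no new data are needed. The Masking section says the biostatistician remains unaware of assignment, so the choice can be recorded before any comparison by arm.

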## Results

Recruitment into the study has proceeded as planned (Table 4). The majority of subjects are self-referred, having heard of the study either through email, flyers, or from a friend or family member. We have had mixed success in recruiting minorities for the study. Advertisements in the Spanish print media and in clinics serving minority populations were added to increase recruitment among the underserved. In addition, our Hispanic research assistant has helped us to recruit representative numbers of Hispanic subjects through personal contacts. Despite adding an African-American research assistant to the team, we have had less success recruiting African Americans.

**Table 4 T4:** Recruitment in the Clinical Feasibility Trial of Craniosacral Therapy (CST) as of January, 2008

	**N**	**Percent**
Inquiries about study	226	
Never reached	45	20.0
Declined/deferred screening	12	7.1
Screened	169	74.9
Eligible, but declined	28	16.6
Ineligible	60	35.5
Headache characteristics	26	43.3
Psychiatric diagnoses	9	15.0
Hormonal issues	9	15.0
Other	16	26.7
Scheduled for consent	81	47.9
Referral pattern		
Health professionals*	28	16.6
Friends/family	28	16.6
Email advertisements†	46	27.2
Local print advertisements§	28	16.6
Flyers/brochures#	14	8.3
Recruitment letter**	6	3.6
UNC Website	1	0.6
Unknown	18	10.6

* Health professionals that referred patients to the study included neurologists, family physicians, and nurses.

† The university allows researchers to recruit subjects through an all-campus email message. The message goes out to students, faculty, and staff.

§ Print media included health-related publications and local English and Spanish-language newspapers

# Flyers and brochures were posted in physician's offices and clinics.

** A letter introducing the study was sent to 1000 adult patients who had been seen in the Family Medicine Center in the past 3 months.

At this time, 169 individuals have been screened for eligibility of which 109 were eligible to take part in the study. Five did not qualify during the baseline phase because of inadequate headache frequency. Nineteen have withdrawn from the study after giving consent. So far, seven subjects have failed to complete their headache diaries. Other subjects have dropped out due to intercurrent medical problems, accidents, or changes in conventional medication. No subject has dropped out due to an adverse event. So far, there has been equal drop out between groups after randomization.

Well over half of our subjects have adhered to completing a data-rich daily diary, either online or on paper, with minimal attrition. So far, we have lost 16% of subjects due to an inability to keep up with daily diary entry. Since the online diaries have been available, 86% have chosen to use them; 14% have chosen the paper diaries.

We have found that the online diary is superior to the paper diary for several reasons: (1) Missing data on the online diaries can be identified earlier and subjects can be prompted to remedy it. The paper diary is completed weekly and mailed in; it is not feasible to have subjects correct missing days once mailed to us. (2) Online diary data goes directly into a text file. Although there is still a potential for subject input error, this method eliminates the errors of secondary data entry. The time required for secondary data input is also eliminated. (3) Perhaps because they can type into it, subjects add more comments to the online diaries. We believe this provides a richer data set. (4) Finally, the online diaries are easier to copy. Several of our subjects have asked for a copy of the diary to share with their provider. Their individual diaries can be extracted from the online diary and sent to them at the end of their participation in the study.

## Discussion

Migraine is a common condition associated with significant disability [2]. Because pharmaceuticals for migraine provide incomplete relief of symptoms and are associated with significant side effects, many individuals seek complementary therapies, such as CST. Up to now, CST has not been studied rigorously. This report supports the feasibility of undertaking a rigorous randomized clinical trial of CST for migraine, using a standardized CST protocol and an innovative control protocol developed for this study.

In any study of complementary therapy in which there is the likelihood of a substantial placebo and expectation effect, a methodology is needed that permits detailed evaluation of the interaction between therapist and subject. We find that the Noldus system of interactional analysis using videotapes of the treatment sessions is a feasible, though time consuming, technique for achieving this goal. A detailed analysis of the videotapes will lead to refinements of the control (LSSM) protocol such that it more closely matches the intervention (CST) in terms of credibility and expectations of benefit. In addition, a qualitative evaluation of the post-intervention interview will yield important information about subject's satisfaction with the therapies.

We have established that it is possible to recruit enough subjects with migraine to obtain comparison groups with sufficient analytic power, though an enrollment period of 18 months would be needed to obtain at least 45 subjects in each group. Our data analyses, comparing CST with LSSM will allow us to determine effect sizes appropriate for a larger, definitive trial.
